## Abstract

**Simple Summary:**

The benefits of regular physical activity on various health variables in older people have been extensively reported in scientific evidence. Resistance training, multi-component training, and walking exercise are the most commonly used physical activity interventions in older people, while interventions with adapted taekwondo are less common but have similar results to the strategies mentioned above. As a result, this study protocol aims to analyze and compare the effects of an adapted taekwondo program with respect to multi-component training and walking exercise on health status in independent older women. Secondarily, we analyze the variability of the inter-individual response and compare it according to the designated training system. According to the current scientific evidence we expect that adapted taekwondo will produce more significant effects and greater inter-individual responses in cognitive status, brain activity, health-related quality of life, and postural balance than the other training methods. If this intervention proves effective, it could be an alternative for older women.

**Abstract:**

This study protocol aims to analyze and compare the effects of an adapted taekwondo program with respect to multi-component training and walking exercise on health status in independent older women. Secondarily, we analyze the variability of the inter-individual response and compare it according to the designated training system. The sample will consist of 64 women between 60 and 65 years, randomly assigned to experimental group 1 (*n* = 16; adapted taekwondo), experimental group 2 (*n* = 16; multi-component training), experimental group 3 (*n* = 16, walking exercise) or control group (*n* = 16; no intervention). The experimental groups will perform the designated training for three sessions (60 min per session) per week over 16-weeks, while the control group will not receive any treatment. The main outcome will provide information about (i) blood pressure, (ii) lipid profile, (iii) frequency of food consumption, (iv) body composition, (v) cognitive status, (vi) brain activity, (vii) health-related quality of life (HRQoL) and (viii) physical-functional fitness. Our hypothesis indicates that adapted taekwondo produces more significant effects and greater inter-individual responses in cognitive status, brain activity, HRQoL, and postural balance than the others training methods. If this intervention proves effective, it could be an alternative for older women.

## 1. Introduction

Scientific evidence has extensively documented the benefits of regular physical activity on various health variables in older people [1,2,3,4,5]. For example, a significant reduction in resting blood pressure and heart rate [4], lower incidence of cardiovascular events [6] and falls [1,2], a significant increase in cardiorespiratory fitness, muscular endurance and strength, flexibility, agility, and dynamic balance [7,8], as well as significant improvements in attention [9] and cognitive processing speed [10]. Facts that, as a whole, favor functional independence and improve health-related quality of life in older people [3,4].

Some of the most recurrent physical activity strategies to intervene in older people correspond to resistance training [1,5], multi-component training [7,11], and walking exercise [6,12], probably because they have greater diffusion, scientific support, and versatility to dose the magnitude of the load and the exercises to the characteristics of the participants [5,13]. Following the above, government-sponsored physical activity programs for older people have reported endurance, strength, flexibility, balance, agility, walking, healthy dancing, and recreational sports as the main activities. However, their average adherence rate reaches 50% [4].

In the same context, physical activity interventions for older people based on Olympic combat sports have reported a mean adherence greater than 80% [8,13,14], with similar physical, physiological, and psychoemotional outcomes to other physical activity intervention strategies such as those mentioned above (resistance training, multi-component training, and walking exercise). Specifically, interventions with adapted taekwondo in older people have reported a significant increase in muscle strength of the lower [9,15] and upper limbs [15], cardiorespiratory fitness [9], flexibility [9], agility and dynamic balance [9,15,16,17], as well as significant improvements in the multidirectional reach test and a significant decrease in the gait stability ratio [17]. Cho and Roh [9] reported a significant increase in brain-derived neurotrophic factor, vascular endothelial growth factor, and insulin-like growth factor-1, while Lee, Scott, Pekas, Lee, Lee and Park [15] reported a significant decrease in resting epinephrine. In summary, taekwondo improves the health status of older people with adherence rates greater than 90% through interventions lasting 11 to 16 weeks [9,15,16,17].

On the other hand, in Chile, more than 70% of people over the age of 60 years old are classified as physically inactive [18], with women having the highest prevalence at 74.2%, and men at 54.7% [18]. Additionally, Chilean women are more sedentary (90%) and have a higher prevalence of overweight/obesity (74.8%) than men, who reach 83.3% and 73.6% for the same variables, respectively [19]. These data represent elements that would have a negative impact on the health status of Chilean older women [20]. Therefore, this study protocol aims to analyze and compare the effects of an adapted taekwondo program with respect to multi-component training and walking exercise on health status (blood pressure, lipid profile, frequency of food consumption, body composition, cognitive status, brain activity, health-related quality of life and physical-functional fitness) in independent older women. Secondarily, analyze the variability of the inter-individual response of the participants and compare according to the designated training system.

Based on previous studies [6,7,8,9,11,12,14,15,16,17] we hypothesized that: (i) adapted taekwondo produces significantly greater effects on cognitive status, brain activity, health-related quality of life, and postural balance than a multi-component training and walking exercise, and; (ii) older women who participate in the adapted taekwondo program have more favorable inter-individual responses (higher percentage of responders) in cognitive status, brain activity, health-related quality of life and postural balance compared to women who participate in a multi-component training and walking exercise.

## 2. Material and Methods

### 2.1. Study Design

The study includes an experimental design (randomized controlled trial), double-blind, repeated measures, four parallel groups (three interventions and one control), and a quantitative approach. The methodology followed will be the Consolidated Standards of Reporting Trials Statement (CONSORT) methodology [21].

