#### 2.6.1. Adapted Taekwondo (TKD) Program

The main part of the TKD program will consist of non-contact activities, distributed in 10 min of basic postures and specific movements with the upper limbs (strikes and blocks) and 20 min of lower limb movements (displacement, postures, kicks) performed individually and in pairs with and without the implementation of taekwondo (shields and impact pads). In addition, choreographies or poomsae (sequence of arm and leg movements that simulate imaginary combat) specific to this modality were adapted to the characteristics of older women for 10 min. The training volume will be quantified by sets and the number of repetitions of the specific movements (i.e., strikes, blocks, displacement, postures, and kicks) with the rest of 2 min between sets. The intensity of the training takes into account the recommendations of previous studies with older people [9,15], so it will remain moderate to vigorous using the percentage of the maximum heart rate (HRmax) of each participant for its control (between 50% and 70% of the HRmax) with a heart rate sensor strap (H10, Polar Electro Oy, Kempele, Finland), which will be live transmitted throughout the protocols (TKD, MCT, and WE) through Bluetooth to a tablet (iPad 4, Apple, Inc., Cupertino, CA, USA) where the participants will be continuously monitored using the Polar Team app version 1.3 (Polar Electro Oy, Kempele, Finland). The rating of perceived exertion will be measured with the Borg scale (maximum value of 10 points). The adapted taekwondo sessions will be led by a Ph.D. student in health and certified as a taekwondo instructor by the National Sports Federation of Taekwondo WT. The sessions will take place in the multipurpose room of gym B of the Universidad Católica del Maule, which has an EVA rubber floor (tatami).

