#### 2.6.2. Multi-Component Training (MCT) Program

The main part of the MCT will consist of 40 min of distributed work in a circuit, including resistance training focused on the large muscles of the upper limbs (i.e., biceps, triceps, deltoids, and latissimus dorsi) and lower limbs (i.e., quadriceps, hamstrings, glutes, and gastrocnemius) combined with exercises aimed at cardiorespiratory fitness, agility and postural control (static and dynamic balance), using elastic bands, poles, 2-kg medicine balls, and chairs, following previous recommendations [4,5,7,11,22]. The training volume will start (the first 4-weeks) with 3 sets of 10 repetitions per muscular exercise with a 2 min rest period between the sets, performing slow movements of two seconds in concentric contraction and four seconds in eccentric contraction [25]. Between weeks 5 to 8, the volume will increase to 4 sets of 10 repetitions per muscular exercise with 2 min of rest between sets. Between weeks 9 and 12, the sets will remain at 4, and the number of repetitions will be increased to 12; finally, between weeks 13 and 16, the number of sets and repetitions (4 × 12) will be maintained reducing the rest time to 90 s. The resistance training intensity will be moderate to vigorous (between 5 to 8 points), controlled with the OMNI-Resistance Exercise Scale of perceived exertion [26]. The intensity of the cardiorespiratory fitness, agility, and postural control will be maintained at moderate to vigorous (between 50% and 70% of the HRmax), controlled with a heart rate sensor strap (H10, Polar Electro Oy, Kempele, Finland), which will be live transmitted through Bluetooth to a tablet (iPad 4, Apple, Inc., Cupertino, CA, USA), and individualized according to the initial assessments of the participants and following previous recommendations [3,5]. Furthermore, the rating of perceived exertion will be used (Borg scale of 10 points). The MCT sessions will be directed by a Master’s student in physical activity sciences with experience working with older people. The sessions will take place in the multipurpose room of gym B of the Universidad Católica del Maule, which has an EVA rubber floor (tatami).

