#### 2.6.4. Control Group (CG)

Regarding the CG, the individuals will participate in the assessments (initial and final) and will be asked to maintain their usual activities of daily living. A research assistant will contact the participants by telephone (once a week) to inquire about their health status and monitor their activities. At the end of the intervention period, the CG will be invited to participate in a physical activity program developed at the University based on the results of this study.

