### 2.7. Outcomes and Procedures

The first meeting with the participants will be held to explain the scope and aim of the study, obtain the signature of informed consent, administer the anamnesis, and randomly assign them to the intervention groups. Next, for a week, the older women will be assessed on the variables considered for the study; later, they will participate in the designated training programs. After 16-weeks of intervention, older women will undergo the same initial assessments for one week. One of the researchers will supervise all the assessments, which will be carried out by an anthropometrist (body composition), a nurse (blood pressure, lipid profile, and frequency of food consumption), a speech-language pathologist (cognitive status and health-related quality of life), a psychologist specializing in neuroscience (brain activity), and two physical education teachers (physical-functional fitness). The evaluators will not have information about the training groups, nor will the participants know their identities (i.e., a double-blind shield). Figure 2 shows a summary of the assessments and sessions that are usually part of the intervention.

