Health-related quality of life: This will be obtained using the Health Survey Short Form (SF-36) version 2, which measures the attributes of eight health dimensions: physical function, physical role, body pain, general health, vitality, social function, emotional role, and mental health [31]. Each dimension is made up of a series of questions that together give a scale ranging from 0 (the worst health status for that dimension) to 100 (the best health status) [31].

Physical-functional fitness: This will be evaluated with the Senior Fitness Test, which allows evaluation of great reliability and easy application [32]. The order of application of the tests contemplated in the battery will be a chair stand test to assess the strength of the lower limbs, counting the number of repetitions made in 30 s. Using a 3-lb dumbbell and counting the number of repetitions made in 30 s, the arm curl test will assess upper-limb strength. A 2 min step test to assess cardiorespiratory fitness, recording the number of knee raises that reach at least an angle of 70° on the hip joint of each participant. The Chair sit-and-reach test to assess the flexibility of the lower limbs, measured in cm. The back scratch test to assess flexibility on the upper limbs, measured in cm. The timed up-and-go test to assess agility and dynamic balance, surrounding a cone at 8-ft (2.44 m) and recording time in seconds.

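### The trial is called double-blind, but participants necessarily know their arm; only evaluator blinding is feasible, so the SF-36 and food-survey results are open-label

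*Protocol article*

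**What the plan says.** All references are to the protocol article.

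- **Label.** Section 2.1 (Study Design): "The study includes an experimental design (randomized controlled trial), double-blind, repeated measures, four parallel groups (three interventions and one control".
- **Meaning of the label.** Section 2.7 (Outcomes and Procedures): "The evaluators will not have information about the training groups, nor will the participants know their identities (i.e., a double-blind shield". This is the only explanation given. Section 2.4 has blinding in its title, but its text covers randomisation only.
- **Timing of assignment.** Section 2.7 has the first meeting explain the study's scope and aim and then "obtain the signature of informed consent, administer the anamnesis, and randomly assign them to the intervention groups". The week of baseline assessments follows.
- **Arms.** Section 2.6.1: "The adapted taekwondo sessions will be led by a Ph.D. student in health and certified as a taekwondo instructor". Section 2.6.2: "The main part of the MCT will consist of 40 min of distributed work in a circuit". Section 2.6.3 describes walking on flat ground. In Section 2.6.4 the controls "will be asked to maintain their usual activities of daily living".
- **Quality of life.** Section 2.7.1, among the primary outcomes: "This will be obtained using the Health Survey Short Form (SF-36) version 2". The same section lists a self-applied eating-habits survey.
- **Hypotheses.** The Introduction expects taekwondo to do better than multi-component training and walking in cognitive status, brain activity, health-related quality of life and postural balance, both in mean effect and in percentage of responders.

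**The concern.** A reader takes double-blind to mean that neither the person assessed nor the person assessing knows the allocation. Group differences in self-reported or effort-dependent outcomes are then read as protected from the participant's expectations and from her wish to do well in the programme she was given. The arms here are openly different activities, so the participant half of that protection cannot exist.

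This affects interpretation because quality of life is one of the outcomes on which the taekwondo claim rests. A reader relying on the label would give an SF-36 difference, or a difference in SF-36 responder percentages, more weight than the design supports. The limitations in the Discussion name adherence and COVID-19 but not unblinded participants, so nothing in the article corrects that reading.

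**Working it through.** The plan gives no figure on this point, so the check compares the label with the design and the outcomes.

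**Step 1. What the participant clause could mean.** The words "nor will the participants know their identities (i.e., a double-blind shield" do not say whose identities are meant.

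- If they mean the evaluators or the other participants, the clause concerns anonymity. It is not blinding to allocation.
- If they mean the woman's own group, the rest of the protocol contradicts it. She is assigned at the first meeting and then attends 48 sessions (3 per week × 16 weeks) of a recognisable activity, or none. No sham activity or masking of the study aim is described.

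On either reading the participants are not blind to treatment.

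**Step 2. What remains.** Evaluators without group information are stated and feasible. One of the two layers implied by the label is present.

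**Step 3. Which primary outcomes lose the claimed protection.**

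| Type of outcome | Domains or tests (Section 2.7.1) | Effect of evaluator blinding alone |
|---|---|---|
| Self-report | SF-36; food survey | The unblinded woman supplies the answer, so participant expectation is not controlled |
| Performance depending on effort | Six Senior Fitness tests; handgrip; also phonetic fluency, the reaction-time task and standing still on the force platform | Partial: running and scoring are protected, the woman's effort is not |
| Little under her control | Lipids; anthropometry | Little affected |

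By domain, 2 of 8 primary domains are self-reported (food consumption and quality of life). Of the 4 hypothesised domains, 1 is self-reported (quality of life). The other three rest at least partly on tasks in the second row.

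**Step 4. Which comparisons are affected.** Both hypotheses set taekwondo against the two other programmes. Women in each of these arms know which programme they received, so the issue reaches the hypothesised comparisons as well as those with the control group.

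**Step 5. Timing.** Assignment comes before the baseline week. Baseline answers and effort may therefore also be given with knowledge of the arm. The article does not say when each woman is told her group, so this is a possibility only.

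**The case against.** The strongest reply is that participant blinding is unattainable when exercise modes are compared, that the feasible safeguard (masked evaluators) is planned, and that the fault is therefore one wrong term. Correcting it alters no randomisation, outcome, sample size or test. Most of this stands: the design should not be faulted for lacking participant blinding. What does not follow is that the label is harmless, because it asserts a protection that a hypothesised self-reported outcome lacks.

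Five stronger readings are tempting, and the document does not support them.

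- **That the problem lies mainly in the comparison with controls.** Both hypotheses compare active arms with the same session frequency and duration in weeks. The control group is in neither.
- **That a known share of the results is compromised.** Such a share depends on how variables are counted. Section 2.7.1 lists roughly 58: 2 blood pressures, 6 lipid measures, 2 food scores, 27 body measures, 1 cognitive survey, 1 EEG, 8 SF-36 scales, 6 fitness tests, 1 handgrip and 4 balance values. The self-reported ones are 8 + 2 = 10, and 10/58 = 17%. That is a count, not an estimate of bias.
- **That the protocol falsely claims blinded instructors.** It names only evaluators and participants.
- **That the main conclusion should move to force-platform balance.** Standing still also depends on the participant, and re-ranking the hypothesised outcomes is a debatable trade-off that a wrong label does not require.
- **That women are told taekwondo is expected to win, or that they will reveal their arm to evaluators.** The article says only that they hear the scope and aim. Disclosure is a risk, not a documented event.

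The absence of a non-disclosure instruction is not counted as an error either, since a condensed article commonly leaves that to the full protocol.

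**Conclusion.** The point holds in a limited form. Sections 2.1 and 2.7 claim double blinding, and the design can deliver evaluator blinding only. The missing protection concerns 2 of 8 primary domains fully (SF-36 and food survey), including 1 of the 4 hypothesised domains. It concerns the effort-dependent tests in part, because masked evaluators still protect how these are run and scored.

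The direction and size of any bias cannot be derived from the document. In particular, nothing allows expectation to be sized between the three active arms. The conclusion rests on two assumptions: that women recognise the activity they perform, and that evaluator blinding is carried out as stated.

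This is more than a clerical slip, because it changes how far the quality-of-life and food-survey results can be trusted. It is not a reason to change the arms, the sample or the outcomes. It should be corrected before results are reported.

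**What to change.** 1. In Sections 2.1 and 2.7, replace double-blind with: assessor-blinded; participants not blinded.
2. Rewrite the clause on identities in Section 2.7 so that it says whose identities are withheld and from whom, and does not present this as blinding to allocation.
3. Ask women not to reveal their group at the final assessment, and have each evaluator record whether it was disclosed. If the full protocol already provides for this, a reference to it is enough.
4. Add to the limitations that participants know their arm, and that SF-36 and food-survey differences, including responder comparisons on them, are open-label results.

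The cost is a few sentences, one instruction to participants and one item per final assessment. Arms, sample size, outcomes and tests are unchanged. The downside is that the design is described less favourably.

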### 2.2. Ethical Approval

The current protocol has been reviewed and approved by the Scientific Ethics Committee of the Universidad Católica del Maule, Chile (approval number: N°29-2022) and developed following the Declaration of Helsinki for work with human beings. In addition, it has been registered in the Clinical Trial Protocol Registry and Results System (ClinicalTrials.gov) of the United States of America (code: NCT05275140; https://clinicaltrials.gov/ct2/home, accessed on 22 April 2022).

### 2.3. Sample Size Calculation

The sample size calculation indicates that the ideal number of participants per group is 16. According to previous studies [22], for this calculation, an average difference of 3.46 repetitions (chair stand test) was used as the minimum difference required for substantial clinical relevance, with a standard deviation of 3.38 repeats, considering an alpha level of 0.05 with 90% power and an expected loss of 15%. GPower software (Version 3.1.9.6, Franz Faul, Universiät Kiel, Kiel, Germany) will be used to calculate statistical power.

